## Abstract

**Background:**

Physical activity (PA) has significant health benefits for older adults. However, many older adults in Hong Kong remain physically inactive. Interventions tailored to one’s current stage of change (SOC) are more effective than non-SOC-tailored ones in facilitating behavioral changes. Chatbots are potentially useful to deliver SOC-tailored interventions to promote PA among older adults.

**Objective:**

This randomized controlled trial (RCT) will compare the efficacy of an SOC- versus a non-SOC-tailored intervention in increasing the prevalence of meeting World Health Organization (WHO)-recommended PA levels 6 months after completion of the intervention among inactive community-dwelling individuals aged ≥65 years.

**Methods:**

This is a partially blinded (outcome assessors and data analysts) and parallel-group RCT. A total of 278 inactive community-dwelling people aged 65 years or more will be randomized evenly into either an intervention group or a control group. In the intervention group, a fully automated chatbot with natural language processing (NLP) functions will measure participants’ SOC related to PA and deliver web-based interventions tailored to their current SOC every week for 12 weeks. In the control group, the chatbot will not measure participants’ SOC but will deliver a non-SOC-tailored web-based intervention every week for 12 weeks. Participants will be interviewed at baseline (T0), after completion of the intervention (T1), and 6 months after T1 (T2). The primary outcome is the prevalence of meeting WHO-recommended PA levels (ie, at least 150 minutes of moderate-intensity aerobic PA, at least 75 minutes of vigorous-intensity aerobic PA, or an equivalent combination of moderate-to-vigorous physical activity [MVPA] every week). PA will be measured using the Chinese version of the International Physical Activity Questionnaire Short Form (IPAQ-SF) and accelerometers at T0, T1, and T2. Secondary outcomes include (1) minutes of MPVA, low-intensity PA, and sedentary time in the past week; (2) step counts in the past week; (3) SOC levels, perceived pros, perceived cons, and perceived self-efficacy related to PA; (4) compliance to the web-based interventions; and (5) cognitive status measured at T0, T1, and T2. Intention-to-treat analysis will be used for data analysis.

**Results:**

Recruitment started in November 2024. By February 2025, a total of 185 participants completed the baseline assessment and were randomly assigned to either the intervention group (n=93, 50.3%) or the control group (n=92, 49.7%). Recruitment will be completed by the end of June 2025. The follow-up assessment at T1 started in March 2025. Data collection is expected to be concluded in February 2026.

**Conclusions:**

The findings will extend the application of SOC and contribute to the evidence of the effectiveness of SOC-tailored and chatbot-delivered interventions. If the chatbot-delivered SOC-tailored intervention is proven effective to increase PA levels, it will require relative less resources to implement and maintain. It can be integrated into the existing WhatsApp groups operated by organizations providing services to older adults in Hong Kong and create public health impacts.

**Trial Registration:**

ClinicalTrial.gov: NCT06641492; https://clinicaltrials.gov/study/NCT06641492

**International Registered Report Identifier (IRRID):**

DERR1-10.2196/68796

## Introduction

### Background

Hong Kong has a rapidly aging population. It is predicted that 22% of Hong Kong residents will be 65 years or older by 2030 [1]. Recent data show that 75% of Hong Kong older adults have one or more chronic diseases [1], which has created a huge burden on the health care system.

Physical activity (PA) is defined as any bodily movement produced by skeletal muscles, resulting in an expenditure of energy [2]. PA is well recognized as an effective intervention for reducing mortality and dependence-inducing diseases [3] and improving cognitive function, frailty symptoms, and physical functions among older adults [4,5]. The World Health Organization (WHO) recommends that older adults without any contradiction of PA do at least 150 minutes of moderate-intensity aerobic PA, 75 minutes of vigorous-intensity aerobic PA, or an equivalent combination of moderate-to-vigorous physical activity (MVPA) every week [3]. However, physical inactivity remains a worldwide phenomenon and increases significantly with age. A systematic review showed that 43.4%-78% of older adults across countries cannot meet the WHO-recommended PA levels [6]. In Hong Kong, the proportion of older adults who did not meet the WHO-recommended PA level increased from 13.5%-42.8% in 2018-2019 [7] to 22.2%-53.3% in 2020-2022 [8]. A recently published study showed that 28.6% of older adults in Hong Kong had a low level of PA in July 2022 [9]. There is a strong need for improvement.

Factors associated with PA among older adults have been well studied. A systematic review suggested that a lack of knowledge, skills, capacities, or support from peers or family members related to PA, the perception that PA would cause pain or injury, difficulties in accessing sports facilities, and concerns related to bad weather are barriers to performing PA among older adults [10]. Perceived benefits of PA on physical and mental health, perceived self-efficacy to perform PA, and suggestions from health professionals have been identified as facilitators of PA in this population [10]. Similar facilitators and barriers apply to older adults in Hong Kong [9]. These factors will be addressed by our interventions.

A number of interventions have been conducted to promote PA among older adults. The majority of them use face-to-face approaches, such as motivational interviewing, PA coaching, and educational sessions [11]. As compared to no or minimum interventions, these approaches increase objectively measured PA levels in both the short term (≤3 months) and the medium term (3-12 months) [11]. However, these interventions require significant personnel and resources to implement. There is an increasing number of web-based interventions for older adults. A systematic review of 18 randomized controlled trials (RCTs) showed that web-based interventions are feasible to promote PA among older adults [2]. Digital PA tracking and feedback (ie, providing automatic tracking and feedback on PA levels based on pedometers/accelerometers/smartphones) and digital PA coaching (ie, goal setting, promoting PA according to participants’ baseline PA situation) were the most commonly used strategies in these RCTs [2]. However, 7 of these RCTs were feasibility trials with limited sample sizes (10-30 per group) instead of full-powered RCTs, and 11 only measured short-term efficacy (≤3 months). Moreover, none of these RCTs was conducted with the Chinese population.

As the most commonly used stage model, the stage of change (SOC) postulates that completed behavioral changes progress through 5 ordinal stages (precontemplation stage, contemplation stage, preparation stage, action stage, and maintenance stage), and individuals require interventions tailored to their current SOC in order to effectively facilitate progression toward sustained behavioral changes [12]. A meta-analysis showed that SOC-tailored interventions are more effective than non-SOC-tailored ones [13]. The SOC has been widely applied to guide PA promotion in different populations [14-23], including older adults [19,20,22,23]. However, most of the SOC-tailored PA interventions use face-to-face approaches (eg, counselling, written material, onsite educational sessions, and motivational interviews) [14-16,18,19,21,23]. It is resource demanding as project staff need to measure the SOC of each participant and prepare and select interventions tailored to their current SOC. To the best of our knowledge, only 2 web-based PA interventions targeting older adults have tried to send some simple tips in text messages tailored to their current SOC [20,22].

Chatbots are computerized programs that replicate human interactions through various forms of communication [24], and they have become increasingly popular in health communication. Systematic reviews have highlighted the feasibility and effectiveness of chatbots in promoting healthy lifestyles, smoking cessation, treatment adherence, and vaccination uptake and reducing substance misuse [25-27]. Two studies applied chatbots to promote PA among office workers in South Korea [28] and adults in the United States [29]. In the South Korean study, the chatbot automatically sent a message to each participant every day to remind them to perform the stair-climbing activity. Once the participant completed the desired activity and notified the chatbot, the chatbot automatically provided positive feedback to the participant. In addition, coffee coupons were given to those who completed this activity. This intervention was shown to be effective in increasing participants’ stair-climbing behaviors [28]. The other study conducted in the United States used a chatbot to provide knowledge and counselling related to PA, which was effective in increasing participants’ daily step count [29]. Chatbots can proactively interact with users to determine their SOC and automatically select a pathway of intervention that is tailored to each user’s current SOC, thus making chatbots ideal for delivering SOC-tailored interventions to promote PA. A previous study demonstrated that applying chatbots to deliver health promotion is feasible and acceptable among older adults in Hong Kong [30].

### Objectives

The proposed RCT will compare the efficacy of an SOC- versus a non-SOC-tailored intervention in increasing the prevalence of meeting WHO-recommended PA levels 6 months after completion of the intervention among inactive community-dwelling individuals aged ≥65 years. Given the strengths of chatbots in health promotion, both the SOC- and non-SOC-tailored interventions will be delivered by a chatbot with natural language processing (NLP) functions. The PA levels will be measured using the validated Chinese version of the International Physical Activity Questionnaire Short Form (IPAQ-SF) and accelerometers.

The secondary objectives of this RCT are to compare the following outcomes 6 months after completion of the intervention between the intervention and control groups: (1) minutes of MPVA, low-intensity PA, and sedentary time in the past week measured using both the IPAQ-SF and accelerometers; (2) step counts in the past week measured using accelerometers; (3) SOC levels, perceived pros, perceived cons, and perceived self-efficacy related to PA; (4) compliance to the web-based interventions; and (5) cognitive status.

## Methods

### Study Design

This is a partially blinded (outcome assessors and data analysts) and parallel-group RCT to be conducted in Hong Kong, China. Inactive community-dwelling people aged 65 years or more will be randomized evenly (1:1) into either an intervention group or a control group. In the intervention group, the chatbot will measure participants’ SOC related to PA and deliver web-based interventions tailored to their current SOC every week for 12 weeks. In the control group, the chatbot will not measure participants’ SOC but will deliver a standard and non-SOC-tailored web-based intervention every week for 12 weeks. Participants will be interviewed at baseline (T0), after completion of the intervention (T1), and 6 months after T1 (T2). The study was registered at ClinicalTrials (NCT06641492). The study flowchart diagram is shown in Figure 1. We will report this trial in accordance with the CONSORT-EHEALTH (Consolidated Standards of Reporting Trials of Electronic and Mobile Health Applications and Online Telehealth) checklist (Multimedia Appendix 1) [31] and the SPIRIT (Standard Protocol Items: Recommendations for Interventional Trials) checklist (Multimedia Appendix 2).

**Figure 1 figure1:**
[figure not shown]
Flowchart of the RCT. RCT: randomized controlled trial; SOC: stage of change.

### Participants and Recruitment

Inclusion criteria are as follows:

Age 65 years or more.Having a Hong Kong identity card.Chinese speaking.Not meeting the WHO-recommended level of MVPA, defined as <150 minutes of moderate-intensity aerobic PA in the past week. The interviewers will assess participants using the validated Chinese version of the IPAQ-SF.Willing to be followed over the phone at T1 and T2.Owning a smartphone.Able to send and read text/voice messages via smartphones.Willing to wear an accelerometer for a week at T0, T1, and T2.

Exclusion criteria include the following:

Blindness or deafnessDiagnosis of major psychiatric diseases (schizophrenia or bipolar disorders) or dementiaScore≥1 in the Chinese version of the Physical Activity Readiness Questionnaire (PAR-Q)Score≤16 in the validated telephone version of the Cantonese Mini-mental State Examination (T-CMMSE) [32]

Participants will be recruited through random telephone calls. Telephone numbers will be selected from up-to-date Hong Kong telephone directories. Trained interviewers will call potential participants over the phone. If there is more than one person in the household who is aged ≥65 years, the one whose birthday is closest to the interview date will be invited for the study to avoid contamination and introduction of extra confounding factors. Interviewers will brief prospective participants about the study and screen their eligibility.

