### Sample Size Planning

At T0, no participant will meet the WHO-recommended PA level according to the inclusion criteria. We assume that 10% of participants in the control group will meet the WHO-recommended PA level at T2 as there are minimum interventions. A target sample size of 97 per group (194 in total) would allow us to detect a between-group difference of 15% in the prevalence of meeting the WHO-recommended PA level at T2 (25% versus 10%; power=0.80, α=.05, PASS version 11.0 [NCSS Statistical Software]). We conservatively estimate the dropout rate to be 30% at T2. Thus, 139 eligible participants per group (278 in total) are required.

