### Measurements

#### Primary Outcome

Prevalence of meeting WHO-recommended levels of PA (at least 150 minutes of moderate-intensity aerobic PA, at least 75 minutes of vigorous-intensity aerobic PA, or an equivalent combination of MVPA every week) is the primary outcome. PA will be measured using the data provided by the participants in the Chinese version of the IPAQ-SF and from the accelerometers (ActiGraph) at T0, T1, and T2. After completion of the baseline telephone survey and before the randomization takes place, participants will be invited to visit our research office to collect the accelerometers. Onsite, participants will be instructed to wear the accelerometers on their waist (ie, above the right hipbone) with an elastic belt for 7 days, including 5 weekdays and 2 weekends, to collect objective data of PA levels. Participants will be asked to wear the accelerometers at all times except when they are showering or swimming. In addition, participants will be reminded to maintain their daily routine when they are wearing the accelerometers. Participants will visit our research office again 1 week afterward to return the accelerometers and recall their PA levels in the past week by completing the Chinese version of the IPAQ-SF. Similar procedures for collecting and returning accelerometers and completing the IPAQ-SF will be arranged after completion of the telephone survey at T1 and T2. The time on and time off related to accelerometer wearing each day will be recorded, and the data will be used to estimate the time spent in sedentary behavior, light PA, and MVPA. To ensure the accuracy of data that represent the habitual PA levels of participants, data from participants whose accelerometer-wearing time is less than 600 minutes per day will be considered invalid. We will calculate the sedentary time, light PA time, and MVPA time using triaxial cut points. The sedentary time, light PA time, and MVPA time have been defined as <200, <1951, and >1952 counts/minute, respectively, with the epoch length being 60 seconds [33]. The chatbot will automatically record the time spent by each participant with it.

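### The inclusion rule is not the complement of the primary outcome, so 0% meeting the WHO level at T0 is not secured by the criteria

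*Protocol article*

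**What the plan says.** Three parts of the protocol article's Methods bear on this.

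- **Participants and Recruitment.** Inactivity is "Not meeting the WHO-recommended level of MVPA, defined as <150 minutes of moderate-intensity aerobic PA in the past week". The instrument is the questionnaire: "The interviewers will assess participants using the validated Chinese version of the IPAQ-SF". Screening is done during the recruitment call. No other criterion limits vigorous activity.
- **Primary Outcome.** Success is "at least 150 minutes of moderate-intensity aerobic PA, at least 75 minutes of vigorous-intensity aerobic PA, or an equivalent combination of MVPA every week". The data sources, used at all three time points, are stated as "PA will be measured using the data provided by the participants in the Chinese version of the IPAQ-SF and from the accelerometers (ActiGraph"). The T0 values come after the telephone survey: participants wear the device for 7 days, then come back to "return the accelerometers and recall their PA levels in the past week by completing the Chinese version of the IPAQ-SF".
- **Sample Size Planning.** "At T0, no participant will meet the WHO-recommended PA level according to the inclusion criteria". The next sentence begins "We assume that 10% of participants in the control group will meet the WHO-recommended PA level at T2", and the calculation then sets 25% against 10%.

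**The concern.** Eligibility and outcome should be mirror images if the trial is to start from zero. They differ in two ways.

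First, the definition. The eligibility rule looks at moderate minutes alone, while the outcome offers two further ways to succeed. Someone can pass the first and already satisfy the second.

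Second, timing and instrument. The screening questionnaire covers a week before the T0 outcome week, and the accelerometer plays no part in eligibility. A low screening week does not fix the result of a later week, still less the result on a different device.

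Anyone already at target who stays there counts as a T2 success without having changed. Such people add the same amount to both arms, shrink the difference that the intervention can produce, and weaken the statement that inactive older adults became active. The Statistical Analysis section does not guarantee a remedy: baseline variables enter the models only when their between-group comparison gives P<.20, so T0 activity may be left out.

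**Working it through.** **1. Does 0% at T0 follow from the written rule?** The outcome's 150:75 ratio implies that one vigorous minute counts as two moderate minutes.

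| Moderate min | Vigorous min | Eligible (moderate <150)? | Moderate + 2 × vigorous | Meets outcome? |
|---|---|---|---|---|
| 0 | 90 | Yes | 180 | Yes (90 ≥ 75) |
| 100 | 40 | Yes | 180 | Yes (combination) |

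Both people satisfy the operational definition of inactivity and already count as successes. The 0% statement is therefore not implied by that definition. A corrected formula would still leave the gap between the screening week and the T0 week, and between questionnaire and accelerometer.

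**2. The plan's own sample size.** Inputs from Sample Size Planning and Statistical Analysis: 10% versus 25%, power 0.80, two-sided α 0.05, dropout 30%. With unpooled variance:

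n = (1.96 + 0.8416)² × [0.10 × 0.90 + 0.25 × 0.75] / 0.15² = 96.8, rounded up to **97** per group.

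Dropout: 97 / 0.70 = 138.6, rounded up to **139** per group, 278 in total.

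Both figures reproduce exactly. T0 prevalence is not a term in the formula.

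**3. What dilution could cost.** The documents do not give the share f of enrolled people who already meet the outcome, so f is an assumption. Suppose also that all of them still meet it at T2 and that 10% and 25% apply to the rest:

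- control rate = f + (1 − f) × 0.10
- intervention rate = f + (1 − f) × 0.25
- difference = (1 − f) × 0.15
- power = Φ( difference / √{[p₀(1 − p₀) + p₁(1 − p₁)] / 97} − 1.96 )

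| f | Control | Intervention | Difference | Power at 97 per group |
|---|---|---|---|---|
| 0% | 10.0% | 25.0% | 15.0 points | 80% |
| 1% | 10.9% | 25.75% | 14.85 points | 78% |
| 2% | 11.8% | 26.5% | 14.7 points | 75% |
| 5% | 14.5% | 28.75% | 14.25 points | 69% |
| 10% | 19.0% | 32.5% | 13.5 points | 59% |

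Example at f = 5%: 0.145 × 0.855 + 0.2875 × 0.7125 = 0.3288; √(0.3288 / 97) = 0.0582; 0.1425 / 0.0582 − 1.96 ≈ 0.49; Φ = 0.69.

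**4. Sensitivity to the assumptions.** If only half of those people still meet the outcome at T2, power is about 73% at f = 5% and 65% at f = 10%. If 10% and 25% already describe everyone enrolled, the rates do not move and power stays at 80% for any f.

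**The case against.** The criterion opens by naming the WHO level, which the article elsewhere defines in full, and the population is repeatedly called inactive. The moderate-minutes definition may be shorthand for moderate-equivalent minutes in a condensed article. That reading is possible. It is not what the definition says, however, and an interviewer would apply the definition as given.

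The power losses rest on stacked assumptions: an unknown f, persistence through 12 weeks of intervention and 6 months of follow-up, and planned rates that apply only to the remainder. The article states its 10% for control participants as a whole, which supports the reading under which nothing is lost. This objection stands, and the figures can only be illustrative.

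Screening one week and measuring baseline in the next is common practice. That also stands: it is no flaw in itself and counts only against the T0 sentence.

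A reader might go further and infer that people already at target have been enrolled, that the sample size is wrong, or that the comparison is biased. The documents support none of these. No T0 prevalence is reported, the 97 and 139 reproduce without a T0 term, and randomization allocates such people to either arm by chance. Taking f to 20% with full persistence would put power at about 43%, but nothing in the article makes that share plausible.

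**Conclusion.** The point holds as an inconsistency between the eligibility rule, the outcome definition and the T0 statement. 0% at T0 is not guaranteed by the criteria, which is different from being shown to be false.

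Validity of the comparison is not at stake. What may suffer is power and the interpretation of the result as uptake from zero. The size is unknown. Under full persistence, with the planned rates applied to the rest, power falls from 80% to 78–75% at f of 1–2%, and to 69–59% at 5–10%. It does not fall at all if the planned rates cover everyone enrolled. This is worth correcting because the planned power leaves no slack, but it is less than a must-fix.

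**What to change.** 1. **Eligibility, for remaining recruits:** define inactivity as IPAQ-SF moderate minutes + 2 × vigorous minutes < 150, the exact complement of the outcome.
2. **Sample Size Planning:** replace the statement that nobody meets the level at T0. Say that participants are below the threshold on the screening IPAQ-SF, and report T0 prevalence separately for the IPAQ-SF and the accelerometer.
3. **Primary model, all participants:** adjust for T0 MVPA measured on the same instrument as the outcome, whatever the P<.20 screen shows.
4. **Sensitivity analysis:** repeat the primary comparison in those below the full threshold at T0 on that instrument.

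Cost: a one-line amendment and a few sentences of analysis text. The T0 data for items 2 to 4 are already planned on both instruments. Item 1 brings a few more screen failures and two eligibility versions in one trial. By the end of February 2025, 185 of 278 participants had been randomized, so it can reach at most 278 − 185 = 93 people. Items 2 to 4 remain useful even if recruitment has closed.
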